#### 2.9.4. Contextual Variables: Concomitant Care, Medication, and External Events

Concurrent services (type, frequency, dosage) will be documented at baseline and weekly; ADHD medication regimen (drug, dose, schedule) and any changes will be recorded weekly for applicable participants. School calendar events and major life changes will be logged to contextualize adherence and outcomes. Analyses will include sensitivity checks stratifying by concomitant care intensity and medication stability (stable vs. changed).

### 2.10. Data Management

Data will be stored securely and with restricted access, in accordance with national and European legislation on personal data protection and the institutional guidelines of the local University. The identity of participants will be protected in accordance with Organic Law 3/2018, of December 5, on the Protection of Personal Data and Guarantee of Digital Rights, and with Regulation (EU) 2016/679, the General Data Protection Regulation (GDPR).

Since the participants are minors, written informed consent will be obtained from their legal guardians, along with signed assent from the minor, after receiving a detailed explanation of the study’s objectives and procedures.

Each participant will be identified by a unique numerical code, used to pseudonymize all collected information. The table of correspondence between codes and identities will be stored in an encrypted file, separate from the consent forms and data files.

Data will be obtained through standardized assessments and automatic logs generated by the DiverAcción website (e.g., number of tasks completed, errors, execution times, or usage metrics). Digital files will be reviewed periodically to verify their integrity and quality before statistical analysis. All digital information will be stored on the University’s institutional cloud storage service, which complies with security standards and guidelines on personal data protection.

Access to the data will be restricted exclusively to authorized researchers, using multi-factor authentication and secure passwords. Physical documents (informed consent forms and administrative records) will be kept in locked filing cabinets on University premises.

Once the study is completed, personally identifiable data will be deleted. Only fully pseudonymized data may be shared for scientific purposes or deposited in public repositories, with the explicit prior consent of the legal guardians.

Legal guardians and participants may exercise their rights of access, rectification, erasure, or objection at any time by contacting the principal investigator as indicated in the study information sheet.

### 2.11. Patient and Public Participation

The development of the DiverAcción telerehabilitation system was carried out using a participatory approach, incorporating the perspectives of end users—adolescents with ADHD, their families, and educational and clinical professionals—from the initial phases of the project.

During the design phase, focus groups were conducted with adolescents, family members, and specialists to identify functional needs, format preferences, digital accessibility barriers, and motivational strategies in therapeutic contexts. These contributions helped define the system’s priority content and functionalities and ensure its relevance and practical applicability. Families also collaborated in reviewing the informational and consent materials, ensuring that the language used was clear, understandable, and appropriate for minors.

In this phase of the feasibility study, participants will not be involved in the methodological design or the analysis of the results, but they will receive regular updates on the project’s progress and its main findings. The study results will be presented to family associations and collaborating entities (educational centers and healthcare services) to facilitate community feedback and guide future steps toward a larger-scale evaluation.

### 2.12. Ethics and Dissemination

The DiverAcción study will be conducted in accordance with the ethical principles of the Declaration of Helsinki and applicable national and international regulations for research involving human subjects. Respect for the autonomy, privacy, and protection of participating minors and their families will be always guaranteed.

The protocol has been approved by the Local Biomedical Research Ethics Committee and complies with the requirements of Royal Decree 192/2023, of 21 March, which regulates medical devices, and Royal Decree 1090/2015, of 4 December, concerning clinical trials with medicinal products.

Since the participants are minors, their inclusion in the study will require the written informed consent of their legal guardians and the minor’s assent, after they have received clear information adapted to their level of understanding about the objectives, procedures, potential risks, and benefits of the study. Participation will be voluntary and may be discontinued at any time without negative consequences.

The DiverAcción telerehabilitation web platform will be provided free of charge by the local University, which will maintain the technical records and version control of the system used for research purposes. A member of the research team will be responsible for the supervision and proper use of the system during the study.

The personal and clinical data of the participants will be processed in a pseudonymous manner and in accordance with current legislation, as detailed in the data management plan included in the Data Management section.

The results of the study will be disseminated through publications in peer-reviewed scientific journals, national and international conferences, and institutional channels of the University of Granada. In addition, informative summaries will be prepared for participating families and associations, with the aim of facilitating the understanding and application of the findings in clinical and educational contexts.

## 3. Discussion

This study aims to examine the feasibility, usability, acceptability, and preliminary functional effects of DiverAcción, a telerehabilitation system designed to enhance planning, organization, time management, and emotional self-regulation skills in children and adolescents with Attention-Deficit/Hyperactivity Disorder (ADHD). The present protocol is part of an incremental development strategy aligned with international recommendations for the evaluation of complex interventions [29,30]. Consistent with our working hypotheses, establishing methodological feasibility and user acceptability is an essential prerequisite before progressing to a randomized controlled trial. A key strength of the intervention lies in its innovative focus on functional cognition within ecologically valid digital environments. Prior research has highlighted the limitations of traditional cognitive training, particularly its weak generalization to real-world contexts. In contrast, DiverAcción integrates gamified, interactive tasks designed to support the transfer of executive strategies to everyday situations, thereby fostering motivation and engagement—factors strongly associated with improved adherence in digital mental health interventions.

A key feature of DiverAcción is its collaborative calendar, designed for daily use in multiple contexts (school, leisure, self-care, family activities). This component not only facilitates planning and time management but also provides an integrated mechanism for promoting transfer to everyday life. Participants categorize each scheduled activity (e.g., school, self-care, leisure, sports), indicate its priority, estimate its duration, and rate its completion, generating objective data on engagement and participation in natural settings. These functionalities were prioritized during the co-design phase with families, participants, therapists, and teachers to ensure their validity and ecological relevance.

The collaborative agenda is conceptually aligned with Toglia’s multicontext approach, which emphasizes generalization through varied environments, explicit transfer criteria, metacognitive training, strategy-focused processing, and engagement in meaningful activities, the collaborative agenda operationalizes guided learning and self-control in multiple everyday contexts to strengthen functional [14,72,73]. In comparison with established occupational therapy programs, such as Cog-Fun (children) and Teen Cog-Fun (adolescents), which offer parent-child metacognitive strategy training in structured weekly sessions and typically assess outcomes using informant-reported measures, such as the Canadian Measure of Occupational Performance (COPM) and the Behavioral Rating Inventory of Executive Function (BRIEF), DiverAcción’s collaborative agenda adds ecologically valid in situ activity traces (e.g., prioritizing, estimating duration, completion) that can complement ratings and support monitoring of real-world transfer [16,17,44,74,75].

Similarly, the parent-centered POET program for preschoolers, delivered in eight sessions, has shown short-term improvements in executive functions and daily routine management, although its assessment relies primarily on parent-reported questionnaires and goal achievement rather than continuous digital recording in naturalistic settings. Therefore, the DiverAcción approach can complement the results of the POET-style approach by capturing objective signals of engagement in different environments [19,21]. In addition to these features, DiverAcción incorporates two scheduled videoconferences, one after the first week and another in the third week, to provide structured feedback and support. If families, teachers, or participants require additional sessions, these can be requested on demand. Furthermore, the platform includes a training section to improve various executive functions, emotional self-regulation, and prospective memory, as well as an integrated communication tool, similar to WhatsApp-style chat, that allows for continuous and direct interaction between participants and professionals throughout the intervention. While these indicators suggest potential transfer beyond the training context, generalization is not directly tested through experimental measures. This limitation should be considered when interpreting the findings, and future studies should include explicit assessments of functional generalization.

In contrast to the assumption that family involvement in DiverAcción is primarily psychoeducational, the protocol incorporates active family mediation and routine-based practice throughout the intervention period. Parents are required to support regular use of the platform and the collaborative agenda, establish consistent daily routines (e.g., homework, personal care, organization of materials), and apply executive and self-regulation strategies in the home context. These aspects are explicitly addressed during scheduled videoconference sessions with parents, where goal setting, supervision strategies, environmental structuring, and family stress management are discussed and adapted as needed. Importantly, family-mediated change is not only encouraged but also monitored through a multi-informant assessment strategy, including parent-, teacher-, and self-reported measures of executive functioning, emotional regulation, time management, parental stress, and perceived parental competence. This approach allows indirect monitoring of family-level and contextual changes over time.

Nevertheless, DiverAcción differs from highly manualized programs such as Cog-Fun and POET in that family-mediated practice is embedded within a flexible, digitally supported framework rather than prescribed through standardized homework protocols with formal fidelity checklists. This distinction should be considered when interpreting generalization processes and highlights an area for further refinement in future controlled trials.

A notable difference from Teen Cog-Fun is the intensity of family involvement. Whereas Teen Cog-Fun includes only two sessions for parents, DiverAcción provides six dedicated sessions (within an eight-session structure) for parents and teachers. It is reasonable to assume that two sessions may not be sufficient to address the substantial parental challenges of raising an adolescent with ADHD, as suggested by Theule et al. [76], who reported lower satisfaction regarding parents’ own achievements in parental self-efficacy. This expanded involvement in DiverAcción aims to strengthen parental competence and reduce stress through ongoing guidance and interactive support mechanisms.

The multidimensional assessment strategy employed—combining feasibility measures, usability, acceptability, satisfaction, and functional outcomes—aligns with prior feasibility studies and strengthens the validity of the evaluation. Automated metrics captured by the platform reduce the risk of observer bias and provide objective indicators of engagement, as recommended in recent digital intervention research. Furthermore, the active involvement of healthcare, educational, and family contexts supports the ecological applicability of the system and increases its potential for real-world implementation. The participatory development process, which incorporated perspectives from adolescents, families, and professionals, also reflects current best practices in user-centered digital health design. However, these aspects should be interpreted as preliminary and descriptive rather than confirmatory, given the exploratory nature of the study.

Several limitations must be acknowledged. First, as a pilot feasibility study, the absence of a control group and the modest sample size limit the ability to draw conclusions about efficacy. Second, external factors inherent to digital interventions—such as variability in access to devices, internet connectivity, and differences in technological proficiency—may influence user performance and engagement. Third, the wide age range (9–17) entails nonlinear changes in executive functioning and emotion regulation-; time versus -eventbased prospective memory places different demands on monitoring and cue use [3,34]. Although ageband delivery, scalable tasks, ER scaffolds, and interface adaptations were implemented, residual variability is likely; future trials should stratify by age and -prespecify PM subtype analyses (event vs. -timebased-) [9,11]. Likewise, SES and maternal education may moderate the development of executive functions, prospective memory, selfregulation, and participation in the intervention; these were not primary in this feasibility phase and justify stratification or a priori adjustment in confirmatory trials- [77,78]. Finally, because recruitment will be limited to a single region, caution is warranted regarding generalizability. Cultural, linguistic, and socioeconomic factors may influence engagement and outcomes; therefore, future trials are planned to incorporate multi-site recruitment, stratified sampling, and cross-cultural adaptation procedures to enhance external validity. These limitations highlight the need for caution when interpreting any observed trends and reinforce the importance of subsequent confirmatory trials. This protocol represents an initial step toward evaluating DiverAcción, focusing on feasibility and acceptability rather than efficacy. The findings will primarily inform improvements to the interface, task structure, and evaluation procedures, supporting the design of a larger randomized controlled trial. Future research should prospectively examine long-term outcomes, mechanisms of change, moderators of response (e.g., ADHD subtype, parental involvement), and implementation factors in clinical and educational settings. Collectively, this work aims to contribute to the development of accessible and ecologically valid digital interventions for adolescents with ADHD, pending further empirical validation.

## 4. Conclusions

This protocol establishes the foundation for evaluating the feasibility, usability, acceptability, and adherence of DiverAcción, a digital intervention designed to improve planning, organization, time management, prospective memory, and emotional self-regulation in young people aged 9 to 17 with ADHD. The combination of gamified tasks, a collaborative daily planner, and a structured psychoeducational program will allow for the collection of precise information on the system’s implementation in real-world contexts. The results are expected to provide preliminary evidence on satisfaction, ease of use, and the intention to continue using the program among children, adolescents, families, teachers, and professionals. Furthermore, the automated metrics will provide objective data that will facilitate the identification of barriers and opportunities for improvement. The findings from this study will guide the necessary adjustments to the platform and inform decisions regarding the feasibility of conducting a randomized clinical trial. In addition, the described methodology offers a replicable framework for future research on telerehabilitation and executive function training in children and adolescents. Taken together, this protocol represents an essential first step in optimizing DiverAcción and moving towards more accessible, effective, and environmentally valid digital interventions for young people with ADHD.

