## 2. Methods

### 2.1. Design

This feasibility study of DiverAcción adopts a quasi-experimental pretest-posttest design without a control group, following the Medical Research Council (MRC) guidelines for complex interventions [29,30] and the SPIRIT 2025 guidelines [26]. This protocol was developed and reported in accordance with the CONSORT extension for pilot and feasibility trials, the SPIRIT 2025 guidelines for trial protocols, and the CONSORT-eHealth checklist for digital interventions [26,27,28]. This is a feasibility trial; a full protocol registration will be completed after analyzing feasibility outcomes and incorporating any necessary adaptations. The trial registry identifier will be provided once the definitive protocol is submitted. The Supplementary Material provides an integrated checklist for each guideline.

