#### 2.4.4. Delivery Format and Dosage

The program will be delivered entirely in a digital, remote format over six weeks. Participants will engage in scheduled online training activities, utilize the digital agenda for planning and organization, and attend synchronous videoconference sessions led by trained occupational therapists. The six-week protocol comprises 12 child/adolescent sessions (two per week) and six parent/teacher sessions (one per week), aligning with the dosage planned for the subsequent randomized controlled trial. In addition to scheduled sessions, participants will be instructed to use the collaborative agenda daily (seven days per week) throughout the intervention to support continuous engagement and transfer of strategies to natural home–school contexts.

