#### 2.9.2. Feasibility Outcomes

The primary aim of this study is to assess feasibility across multiple domains, following established frameworks for pilot and feasibility trials [52,67,68]. Progression criteria for feasibility outcomes are summarized in Table 3 and Figure 2.

The following outcomes will be evaluated:

*Recruitment and Retention*

Recruitment will be measured as the proportion of eligible participants who consent to participate, and the average recruitment rate per month. Retention will be defined as the percentage of participants who complete all planned assessments at T1 (post-intervention) and T2 (follow-up).

*Data Completeness and Missing Data*

Data completeness will be calculated as the proportion of participants providing valid data for each measure at each time point. Patterns and reasons for missing data will be documented. This information will inform the feasibility of data collection procedures and guide refinements for a future trial. Primary feasibility analyses will use complete cases. Sensitivity analyses using multiple imputation may be performed for exploratory clinical outcomes, but the results will be interpreted with caution given the small sample size.

*Adherence*

Adherence will be assessed based on three components:(a)use of the digital agenda on at least 80% of intervention days (over 6 weeks),(b)completion of at least 80% of scheduled online training activities, and(c)attendance at 100% of planned videoconference sessions.

Adherence will be reported as the proportion of participants meeting these criteria.

*Intervention Fidelity*

Fidelity will be ensured through a structured process: all occupational therapists delivering the intervention will complete a 20-h training course prior to implementation, covering theoretical foundations, intervention procedures, and use of digital tools. Fidelity will be monitored using session checklists, regular supervision meetings, and ongoing remote support. Fidelity will be categorized as high (≥80% of protocol elements delivered), moderate (60–79%), or low (<60%).

*Acceptability and Usability*

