**Figure 3 healthcare-14-00323-f003:**
[figure not shown]
CONSORT Flow Diagram Adapted for Feasibility Trials. It will be completed after the collection.

**Table 1 healthcare-14-00323-t001:** DiverAcción Program Structure by Target Group.

Dimension	Frequency	Main Aim	Description	Administered To
Collaborative Agenda	Daily (7 days/week)	Promote planning and monitoring in natural contexts	Participants co-design a personal agenda to schedule daily activities, prioritize tasks, estimate duration, and monitor completion.	Children/Adolescents
Training Sessions	12 sessions (2/week, 45 min each, 6 weeks)	Develop executive skills and emotional regulation through gamified tasks	Virtual sessions focused on planning, organization, time management, and emotional self-regulation using interactive exercises.	Children/Adolescents
Psychoeducation Sessions	6 sessions (1/week, 45 min each, 6 weeks)	Support generalization and caregiver mediation	Sessions for parents and teachers to reinforce strategies, manage routines, and reduce stress.	Parents/Teachers
Therapeutic Support	Continuous (chat/email) + 2 videoconferences (weeks 1 and 3)	Provide guidance and resolve doubts	Integrated communication tools and scheduled videoconferences to monitor progress and address questions.	Children/Adolescents & Parents/Teachers

**Table 2 healthcare-14-00323-t002:** Variables, instruments and timing of administration.

Variables	Instruments	Time Data Collection	Administered to:
Previous experience with digital interventions, sociodemographic, educational and economic data of children and adolescents, pharmacological treatment, other behavioral or psychoeducational interventions	interview	T0	Parents
Preferences regarding digital intervention format	interview	T0	Children and Adolescents
Symptom severity in inattention, hyperactivity–impulsivity and oppositional behaviors (not for subtype classification)	SNAP-IV	T0	Parents
Therapeutic attitudes of professionals towards technology	e-TAP-T	T0	Teachers Occupational therapists
IQ estimated	WASI-II	T0	Children and Adolescents
Feasibility	Automated metrics recorded by the platform: adherence, number of uses, sessions, time of use, errors	T1	Children and Adolescents Parents Teacher Occupational Therapists
Acceptability	TAM questionnaire	T1	Children and Adolescents Parents Teacher Occupational Therapists
Usability	SUS	T1	Children and Adolescents Parents Teacher Occupational Therapists

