User-friendly design	Visual analog scale from 1 to 10	T1	Children and Adolescents Parents Teacher Occupational Therapists
Participant satisfaction	Participant Satisfaction Questionnaire	T1	Children and Adolescents Parents Teacher Occupational Therapists
Therapeutic Alliance	WAI-I	T1	Children and Adolescents
Executive functioning	BRIEF-2 for parents and teachers TEXI Inventory	T0, T1, T2	Parents and Teachers Children and Adolescents
Time management of children and adolescents	Time-S questionnaire EMT	T0, T1, T2	Children and Adolescents Teachers
Prospective Memory	PRMQ-C Automated metrics recorded by the platform	T0, T1, T2 T1	Children and Adolescents
Emotion regulation strategies in everyday life	ERQ-CA	T0, T1, T2	Children and Adolescents
Health-related quality of life (HRQoL)	KIDSCREEN-52	T0, T1, T2	Children and Adolescents
Parents’ perceptions of their parenting competence	BPSES	T0, T1, T2	Parents
Parental stress levels	PSI-4-SF	T0, T1, T2	Parents

Note: T0 = baseline, T1 = immediately post-intervention, T2 = 3 months after intervention.

**Table 3 healthcare-14-00323-t003:** Progression Criteria for Feasibility Outcomes.

Domain	GO (Proceed)	AMEND (Modify)	STOP (Do Not Proceed)
Recruitment	≥70% of eligible approached	50–59%	<50%
Retention	≥80% at T1/T2	60–79%	<60%
Data completeness	≥80% completeness	70–79%	<70%
Adherence	≥80% agenda & training; 100% videoconferences	60–79% agenda/training	<60% agenda/training
Fidelity	≥80% protocol elements delivered	60–79%	<60%
Acceptability (TAM)	Mean ≥ 3.5	Mean 3.0–3.49	Mean < 3.0
Usability (SUS)	Score ≥ 68	Score 60–67	Score < 60
Dropouts	≤20% dropout rate	21–29% dropout rate	≥30% dropout rate

Note. GO = criteria met for progression to definitive trial; AMEND = criteria met with modifications; STOP = criteria not met. Predefined success thresholds were based on widely used benchmarks in feasibility research, such as ≥80% session completion [69], SUS ≥ 68 [55], and TAM mean ≥ 3.5 [70].

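### Table 3 reads consent and retention from a study in which every family gets the programme as GO for a randomised trial, with nothing collected on willingness to be randomised

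*Protocol article*

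**What the plan says.** Section 2.1 (Design) states that the study "adopts a quasi-experimental pretest-posttest design without a control group". Section 2.4.2 gives the training sessions to each participant, and section 2.12 says the platform is free of charge.

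Section 2.9.2 defines the recruitment outcome: "Recruitment will be measured as the proportion of eligible participants who consent to participate, and the average recruitment rate per month". Retention is the percentage completing all planned assessments at T1 and T2. Table 3 sets these bands:

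- **Recruitment:** GO at 70% or more, AMEND at 50–59%, STOP below 50%.
- **Retention:** GO at 80% or more, AMEND at 60–79%, STOP below 60%.

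The note to Table 3 reads "GO = criteria met for progression to definitive trial". The article says more than once that the next trial is randomised. Section 2.4.4, for example, describes the dosage as "aligning with the dosage planned for the subsequent randomized controlled trial", and section 4 says the findings will "inform decisions regarding the feasibility of conducting a randomized clinical trial".

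Table 2 lists one preference item, "Preferences regarding digital intervention format", which section 2.8.4 explains as online, face-to-face or hybrid. The TAM questionnaire concerns acceptance of the platform. The limitations in section 3 link the missing control group to efficacy conclusions only.

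**The concern.** Families here consent to an offer in which receiving the programme is certain. A randomised trial offers a chance of receiving it. Some families who accept the first offer may refuse the second, and the study as described records nothing that would show how many. Retention has a related gap: the figure comes entirely from families who received the programme, whereas a randomised trial also needs T1 and T2 data from families who were allocated to something else.

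Table 3 carries both rates to the definitive trial without qualification. Someone applying it as written would take guaranteed-programme consent as evidence that a randomised trial can recruit. At stake is a decision to proceed, and a recruitment forecast for the larger trial, that rest on a rate measured under a different offer.

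**Working it through.** **No stated figure is numerically wrong.** The article gives no formula-based number to reproduce on this point; section 2.7 sets n = 30 without a power calculation. The check is what the Table 3 rates estimate and how far they carry over.

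**Inputs from the article:** recruitment GO 70% and STOP below 50%; retention GO 80% and AMEND 60–79%; n = 30.

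**Inputs assumed, because the article gives none:** w, the share of consenting families who would also accept randomisation; and control-arm retention.

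**Step 1, recruitment.** Randomised-trial consent = observed consent c × w. At c = 0.70, exactly on the GO boundary:

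| w | 0.70 × w | Table 3 band |
|---|---|---|
| 1.0 | 70% | GO |
| 0.9 | 63% | none (Table 3 assigns no band to 60–69%) |
| 0.8 | 56% | AMEND |
| 0.7 | 49% | STOP |
| 0.6 | 42% | STOP |

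**Step 2, break-even values.** GO is lost when w < 0.70/c, and STOP is reached when w < 0.50/c.

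| Observed consent c | GO lost if w is below | STOP if w is below |
|---|---|---|
| 70% | 0.70/0.70 = 100% | 0.50/0.70 = 71.4% |
| 80% | 0.70/0.80 = 87.5% | 0.50/0.80 = 62.5% |
| 90% | 0.70/0.90 = 77.8% | 0.50/0.90 = 55.6% |

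The result is sensitive near the boundary and less so at high observed consent.

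**Step 3, retention.** With 1:1 allocation, pooled retention = (programme arm + control arm)/2. Starting from 80% in the programme arm:

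- control arm 60%: (80 + 60)/2 = 70%, AMEND;
- control arm 70%: (80 + 70)/2 = 75%, AMEND;
- control arm 80%: 80%, GO;
- control arm 90%: (80 + 90)/2 = 85%, GO.

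The pooled figure can move either way, and the article gives no information on which is likelier.

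**Step 4, sampling error, a separate matter.** If 24 of the 30 participating families said they would accept randomisation (80%), the exact 95% interval would be 61% to 92%. A willingness question would give a rough figure, so it should be reported with its interval.

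**The case against.** The strongest reply is that a single-arm test of deliverability before a randomised study is a legitimate step, and that the article does not claim more. Section 3 says the findings will mainly inform changes to the interface, tasks and evaluation procedures, and section 4 says they will inform the randomised-trial decision. Table 3 has eight rows, ranks none of them and gives no rule for combining them. The article is also cautious about generalising from a single region. Much of this stands.

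Three stronger readings are tempting and are not supported:

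- **That the study alone decides whether the randomised trial goes ahead, or that GO on these two rows launches it.** The article describes one input to that decision and several other criteria.
- **That observed retention is an upper bound.** Participants here carry twelve sessions, daily agenda use and six parent/teacher sessions. Controls might carry much less, and a waiting-list control could be held by the prospect of treatment. On the other side, T1 requires attendance in person, and controls would be asked to attend without having had the programme. The direction is unknown.
- **That consent is overstated by some known amount.** The comparator for the randomised trial is not described, and w comes from no document. With an active comparator the loss could be small.

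The article is also a condensed account, and Figure 2, cited for the progression criteria, is not visible. The absence of a willingness item is therefore established only for the variables listed in the text and Table 2. Even so, Tables 2 and 3 are the article's own list of measures and its own progression rule, and nothing in the text qualifies the recruitment or retention rows. The limitations discuss the missing control group for efficacy and leave these rows out.

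**Conclusion.** The point holds in a limited form. Table 3 applies single-arm consent and retention to progression towards a randomised trial, and no listed variable bridges the gap.

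- **Recruitment:** observed consent may overstate what a randomised trial would achieve, by an amount this study cannot estimate. It carries over unchanged only if every consenting family would also accept randomisation (w = 100%). A result just at GO would be at STOP if more than about 29% of consenters (100 − 71.4 = 28.6) declined randomisation. These figures illustrate sensitivity under an assumed w and predict nothing.
- **Retention:** the observed rate is uninformative about a control arm, and no direction of bias can be claimed.

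The choice of a single-arm design is not at fault. What needs correcting is the unqualified conclusion attached to GO on these two rows, and the missed opportunity to ask a question that costs almost nothing.

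**What to change.** 1. Add one item to the existing T0 parent interview and to the recruitment telephone call: would the family take part, and attend T1 and T2, if allocated by chance to DiverAcción or to the comparator envisaged for the randomised trial? Ask families who decline only where they are reached and where ethical approval covers it.
2. Report that proportion with a confidence interval beside the observed consent rate, as supporting information for the randomised-trial decision. Keep observed consent as the Table 3 criterion. Its thresholds were set for an observed rate, and a hypothetical answer should not become a GO/STOP determinant.
3. State in the Table 3 note and in the limitations that GO on recruitment and retention shows single-arm deliverability only, and that acceptance of randomisation and control-arm retention remain untested.

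**Cost:** one interview question and a few sentences of text, with no extra visit or participant. Stated willingness is hypothetical and may differ from behaviour, the question requires the team to describe a provisional comparator, and asking decliners may need a minor ethics amendment.
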